##### Usual Care Services

Participants in the intervention and control clusters will have access to a range of evidence-based HIV prevention services offered in the county, including Global Fund–supported services, such as HIV testing services, syndromic management of sexually transmitted infections, family planning and postviolence care services; ongoing DREAMS programming; and PrEP [56]. Participants in both arms receive information about available services and are referred to these services upon request. PrEP is available to adolescent girls and young women aged ≥15 at >100 MoH facilities throughout the county [57], and all the participants who choose to use PrEP in the study can access it through these MoH facilities. In keeping with our study design, this choice of usual services as the comparator condition is realistic, ethical, and relevant [58] because it represents a wide range of evidence-based services to reduce HIV risk. However, PrEP uptake and persistence have been suboptimal in this context, indicating that the intervention is warranted, and that the comparator condition is not sufficiently robust to preclude our ability to detect an effect [59].

#### Data Collection

Data collection visits occur simultaneously in each pair of wards at enrollment, and months 3, 6, and 12 (Table 3). At enrollment, interviewer-administered questionnaires are used to assess sociodemographics, relationship characteristics, IPV, behavioral HIV risk factors, and history of PrEP use. Measures are repeated in follow-up questionnaires to document changes in relevant characteristics, attitudes, and behaviors.

DBS samples are collected via fingerprick at months 6 and 12 from all participants who report initiation or continuation of PrEP since the last visit. For participants who report discontinuation of PrEP, reasons for discontinuation are recorded, but DBSs are not collected. Due to storage and transport challenges, DBS samples are also not collected for participants who have relocated outside the county and have follow-up visits conducted by phone or at a remote location. DBS samples are stored in freezers at the IRDO laboratory and then shipped to the laboratory at the University of North Carolina Center for AIDS Research Clinical Pharmacology and Analytical Chemistry Core for quantification of drug concentrations by liquid chromatography-tandem mass spectrometry technology [60].

**Table 3 table3:** Participant timeline.

Procedures			Month 0 (BL^a^)		Month 1		Month 2		Month 3 (3 MFU^b^)		Month 4		Month 5		Month 6 (6 MFU)		Month 7		Month 8		Month 9		Month 10		Month 11		Month 12 (12 MFU)
Assess and confirm eligibility			✓																								
Informed consent			✓																								
Enrollment			✓																								
Locator information and update			✓						✓						✓						✓						✓
**Quantitative data collection**																											
	Sociodemographic and behavioral characteristics	✓						✓						✓												✓	
	PrEP^c^ use history	✓						✓						✓												✓	
	IPV^d^ history	✓						✓						✓												✓	
	Hypothesized mechanisms of action^e^	✓						✓						✓												✓	
	Laboratory assessment (dried blood spots)													✓												✓	
**Tu’Washindi intervention**																											
	Community sensitization session (weekly)			✓		✓		✓																			
	Buddy Days							✓																			
	Support clubs (once or twice per month)			✓✓^f^		✓✓^f^		✓		✓		✓		✓													
**Qualitative data collection**																											
	In-depth interviews (subset of participants)													✓												✓	
**Safety monitoring**																											
	Standardized assessments							✓						✓												✓	
	Short in-person or telephone contact visit																			✓							
	Reporting of IPV, injuries, social harms, or other relevant concerns			✓		✓		✓		✓		✓		✓		✓		✓		✓		✓		✓		✓	

^a^BL: baseline appointment.

^b^MFU: month follow-up appointment.

^c^PrEP: preexposure prophylaxis.

^d^IPV: intimate partner violence.

^e^Also part of process evaluation.

^f^Two support clubs per month.

### Process Evaluation Component

#### Overview

The mixed methods process evaluation uses implementation data; quantitative adolescent girls and young women participant questionnaires; exit surveys with men who attend intervention activities; qualitative in-depth interviews (IDIs) with adolescent girls and young women participants, their male partners, and intervention providers; and a project diary. Our process evaluation framework (Figure 3 [61]) highlights the key evaluation components, relationships between them, and key measures and data sources [62-65].

**Figure 3 figure3:**
[figure not shown]
Process evaluation framework and key measures. Adapted from the Medical Research Council guidelines for process evaluation of complex interventions [60]. IPV: intimate partner violence; MoH: Ministry of Health; PrEP: preexposure prophylaxis; SAB: Stakeholder Advisory Board; TAC: Technical Advisory Committee; YAB: Youth Advisory Board.

#### Participants and Eligibility

Eligibility criteria for adolescent girls and young women participants are described in the Eligibility Criteria section. Participants in exit surveys or male partner IDIs must be males aged ≥15 years. In addition, the exit survey participants must have attended a study Buddy Days or community sensitization event and have been present for at least half of the event, while IDI participants must be a sexual partner of the adolescent girls and young women clinical trial participant and that adolescent girls and young women participant must have provided permission for the study staff to contact the male partner. Intervention providers must be aged ≥18 years and have been involved in delivering Tu’Washindi intervention activities. In addition, all participants must be fluent in English, Dholuo, or Kiswahili; willing and able to provide informed consent; and not have any condition that the site PI or designee determines would preclude participation.

#### Participant Selection and Recruitment

##### Exit Surveys

At all intervention sites, all men who attend a Buddy Days event as a couple are approached while waiting for incentive distribution and asked to complete a survey. A research assistant approaches about 20% of men who attend community sensitization events and asks them to complete survey after the event.

##### In-Depth Interviews

For each of the 5 intervention and control ward pairs randomly selected for qualitative research, we use data captured at month 3 to purposively select a subset of adolescent girls and young women participants (n=30; 4 per intervention ward and 2 per control ward) who are behaviorally eligible for PrEP, per self-report, and have attended at least one support club meeting (intervention wards only). We aim to ensure representation of PrEP users and nonusers and those with and without a history of IPV. Participants who are selected for IDIs are contacted by a research assistant before their month 6 visit, informed that they have been selected, and invited to participate in the IDI.

On the basis of the information provided by the adolescent girls and young women at the month 6 visit, we purposively select male partners (n=20; 4 per intervention ward) for IDIs to represent a range of exposure to the Buddy Days and community sensitization activities.

Male partners are only contacted with the permission of the adolescent girls and young women participants, who provide contact information. A research assistant then contacts the male partner and invites him to participate in the IDI. Study staff do not disclose the PrEP use status of adolescent girls and young women participants to any partner whom they recruit for the IDIs.

Intervention providers are purposively selected for IDIs by the study coordinator to represent a variety of job functions, including mentors, community organizers, counselors, and clinicians (n=20, 4 per intervention ward).

#### Data Collection

Implementation data includes staff hiring and training records; minutes from youth advisory board, stakeholder advisory board, and technical advisory committee meetings; and study activation checklists to track activities, materials, and systems required for successful implementation, such as community introductions, final intervention manuals, and vetted lists of referral agencies. Providers maintain activity logs and attendance records for each meeting or event, and supervisors record minutes from feedback and coaching meetings. Quality and fidelity of intervention activities is documented on observation forms as described above.

Participant questionnaires are administered to adolescent girls and young women participants at each visit to assess mechanisms of change (for all participants) and perceived intervention quality (intervention arm) or potential contamination (control arm). The hypothesized mechanisms of change include PrEP self-efficacy and outcome expectations, PrEP knowledge, healthy communication, disclosure of PrEP use to male partner and partner reaction, community knowledge of PrEP, PrEP stigma, and social assets.

Exit surveys are brief, anonymous, quantitative, interviewer-administered questionnaires that gather information on men’s views of PrEP, their willingness to support their partner’s PrEP use, and feedback on intervention activities.

IDIs are conducted in a private location and facilitated by trained female interviewers following a semistructured guide as follows:

Serial IDIs with adolescent girls and young women participants are conducted at 2 time points (months 6 and 12). Key topics include relationship quality and experiences of IPV, patterns of PrEP use and barriers and facilitators to PrEP access and use, experiences with the intervention, and perceptions of how the intervention has affected the hypothesized mechanisms of change and study outcomes.Male partner IDIs take place at the end of the intervention period and explore men’s experiences with the intervention. Interviews also aim to identify mechanisms through which their attitudes toward PrEP were shifted, or reasons why they were not.Intervention provider IDIs are conducted at the end of intervention delivery to elicit their perceptions of the adequacy of inputs (eg, training and resources), fidelity and quality of delivery, and challenges and perceived benefits to delivering each intervention component.

A program diary is maintained by the study coordinator to record external events (eg, elections, police activity, festivities, and health campaigns) and internal events (eg, increased funding or supply shortages) that may affect intervention delivery or study outcomes. Before intervention implementation in each ward, the study coordinator identifies a set of sources, including study staff, health facility personnel, community members or others who are well-positioned to provide this contextual information, and contacts them at regular intervals to record any updates.

### Data Management

Most questionnaire data are collected on tablets using REDCap (Research Electronic Data Capture; Vanderbilt University) or collected on paper forms and entered into REDCap at the study offices, with hard copies securely stored at the field site [66,67]. RTI implements a quality assurance plan, including routine generation of quality control reports by the data manager and communication of findings for resolution. IDIs are audio-recorded, with debriefing reports completed immediately after each interview and quickly shared with the study team to highlight preliminary findings. Interviews are translated and transcribed at the study site. Electronic copies of forms are securely transmitted to RTI and reviewed for quality control, with weekly query resolutions.

### Sample Size Considerations

The study is powered to identify an absolute difference of 15% between intervention and control arms for the primary outcomes: the proportion with effective PrEP use at month 6 and month 12. Power calculations are conducted using simulations based on the logistic model with normally distributed ward (cluster) effects and assuming 11 wards per treatment arm with type 1 error of 0.025 to account for separate analyses at each of 2 time points. With 60 participants per ward, we will have ≥80% power to detect a 15% difference in the outcome as long as the SD for ward variation is ≤10% and the level of effective PrEP use in control wards remains <50% (far higher than observed in recent trials and demonstration projects). To allow for up to 20% loss to follow-up, our total sample size will be 1584 participants: 72 adolescent girls and young women in each of the 22 wards (11 wards per arm).

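### Enrolling 72 per ward covers 16.7% loss, not the stated 20%, if 60 per ward are to remain (minor error in a stated figure)

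*Protocol article*

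**What the plan says.** All the figures stand in one paragraph of the protocol article, under Sample Size Considerations.

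- Target effect: "The study is powered to identify an absolute difference of 15% between intervention and control arms for the primary outcomes".
- Design and error rate: "assuming 11 wards per treatment arm with type 1 error of 0.025 to account for separate analyses at each of 2 time points".
- Power condition: "With 60 participants per ward, we will have ≥80% power to detect a 15% difference in the outcome", subject to limits on ward variation and on the control-arm level.
- Enrolment: "To allow for up to 20% loss to follow-up, our total sample size will be 1584 participants", broken down as "72 adolescent girls and young women in each of the 22 wards (11 wards per arm".

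No other section gives a different number analysed per ward or a different rule for inflating it. The Design section repeats the target as approximately 72 per ward and 1584 overall.

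**The concern.** The power condition is a number analysed: 60 per ward. The enrolment figure is presented as what is needed to protect that number when as many as one participant in five is lost. Loss to follow-up is a share of those enrolled, so the inflation should divide by the proportion retained. The stated 72 is what results from adding 20% to 60, which protects against a smaller loss.

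At stake is whether the stated tolerance can be used to judge the trial. If achieved loss falls between 16.7% and 20%, a reader relying on this paragraph would conclude that the 60 per ward still holds when it does not.

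**Working it through.** **Inputs**, all from Sample Size Considerations: 60 per ward for power, loss of up to 20%, 72 enrolled per ward, 22 wards (11 per arm), 1584 in total, difference of 15 percentage points, type 1 error 0.025, ward SD of at most 10%, control level below 50%.

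**Step 1. Reproduce the plan's figure.**
- 60 × (1 + 0.20) = 72 per ward, and 72 × 22 = 1584. This matches exactly.
- 60 / (1 − 0.20) = 75 per ward, and 75 × 22 = 1650. This does not match. The gap is 3 per ward, or 66 in total, which is too large for rounding.

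**Step 2. Apply the stated loss to the stated enrolment.**
- Per ward: 72 × (1 − 0.20) = 57.6.
- Total: 1584 × 0.80 = 1267.2, against 60 × 22 = 1320.
- Shortfall: 2.4 per ward, about 53 participants, or 4% of the number assumed for power.

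**Step 3. Find the loss that 72 per ward does cover.**
- 1 − 60/72 = 12/72 = 16.7%.

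**Step 4. Size the effect on power.** I used a cluster-level approximation with k = 11 wards per arm, m analysed per ward, ward SD s on the proportion scale, and p0 and p1 = p0 + 0.15 as the arm proportions:

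Var(difference) = [2s² + (p0(1 − p0) − s²)/m + (p1(1 − p1) − s²)/m] / k

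Worked example with s = 0.10, p0 = 0.40, p1 = 0.55. The two binomial terms sum to (0.24 − 0.01) + (0.2475 − 0.01) = 0.4675.
- m = 60: (0.0200 + 0.4675/60)/11 = (0.0200 + 0.00779)/11 = 0.002527, SE = 0.05026.
- m = 57.6: (0.0200 + 0.4675/57.6)/11 = (0.0200 + 0.00812)/11 = 0.002556, SE = 0.05056.

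The standard error rises by about 0.6%. At m = 60 the between-ward term supplies 0.0200/0.02779 = 72% of the variance, and it does not depend on m. That is why losing 2.4 participants per ward matters little.

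Fall in power from 60 to 57.6 per ward, at two-sided alpha 0.025, across a normal reference and t references with 16 or 20 df:

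| Control level | Ward SD 8 points | Ward SD 10 points |
|---|---|---|
| 5% | 0.2 point | 0.2 to 0.3 point |
| 20% | 0.4 to 0.5 point | 0.4 to 0.5 point |
| 40% | 0.5 to 0.6 point | 0.5 to 0.6 point |
| 49% | 0.5 to 0.6 point | 0.5 to 0.6 point |

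The full range over control levels from 5% to 49% is 0.16 to 0.65 point, which is about 0.2 to 0.7.

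**The case against.** The case on the other side is about importance, since the arithmetic is not open to dispute.

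- **The 20% is a ceiling.** The Missing Data section treats rates above 10% as more than anticipated, so the planning expectation lies within the 16.7% that 72 per ward does cover. This stands, and it makes the shortfall unlikely to bite. It does not make the sentence right, because a tolerance of up to 20% includes 20%.
- **Nothing operational turns on it.** The Results section reports 1150 of 1584 enrolled and 16 of 22 wards complete as of December 2024. No analysis or decision rule depends on the allowance. This stands, and it is why the point is minor and why more enrolment is not requested.
- **Does this show that the stated power is wrong?** A reader might infer that the trial is materially underpowered, or that the claim of at least 80% fails. The document does not support either inference. The paragraph says power came from simulation under a logistic model with normal ward effects, but it does not state sidedness, the test's reference distribution or fully the scale of the ward SD. Those choices move an approximate power level by several points, far more than the effect at issue. Only the difference between 60 and 57.6 per ward is used here, and the 80% claim itself was not tested.
- **Do missing blood samples shrink the allowance further?** The Data Collection section says that "DBS samples are also not collected for participants who have relocated outside the county" and are followed by phone or at a remote site. A PrEP user in that position could remain in follow-up without the biomarker that defines the primary outcome. The article gives no relocation rate and does not say how such a participant is classified, and planned relocation is an exclusion criterion. This can only be an unquantified side note.

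**Conclusion.** The stated allowance is wrong as written, and the error is minor. Enrolling 72 per ward preserves the 60 used for power up to 16.7% loss. At the stated 20% it leaves 57.6 per ward, about 1267 participants against 1320. This rests only on figures in the paragraph and on reading loss as a proportion of those enrolled, and no section defines it otherwise.

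The cost in power is about 0.2 to 0.7 percentage point. That size is approximate and assumes two-sided alpha 0.025, a ward SD of 8 to 10 points on the proportion scale, and control levels of 5% to 49%. It supports correcting a figure. It does not support a conclusion that the trial is materially underpowered.

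**What to change.** Change one sentence in Sample Size Considerations and enrol no one extra. Either:

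1. state that 72 per ward (1584 in total) allows for up to 16.7% loss while keeping 60 per ward; or
2. keep the 20% figure and restate the power from the trial's own simulation at 57 to 58 analysed per ward.

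Option 1 needs no new computation, and its only cost is a slightly less favourable stated tolerance. Option 2 needs one rerun of an existing simulation, with a very small expected change in the result.

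Optionally, describe the allowance as loss of primary-outcome data, so that it is clear whether participants followed remotely without a blood sample count against it.

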### Data Analysis: Clinical Trial

#### Outcomes and Hypotheses

The primary outcomes of the study will be the proportion of study participants with effective PrEP use, defined in Table 4, evaluated immediately postintervention, at month 6, and at month 12 to gauge the persistence of intervention effect. TFVdp levels will be dichotomized by Clinical Pharmacology and Analytical Chemistry Core laboratory specialists to delineate between consistent (≥4 doses per week) versus inconsistent (<4 doses per week) adherence [68]. The aim 1 hypothesis is that the proportion of participants with effective PrEP use at (a) month 6 and (b) month 12 will be *higher* in the intervention versus control arm.

**Table 4 table4:** An overview of key measures for the cluster randomized controlled trial, collected at enrollment and months 3, 6, and 12, unless otherwise noted.

Measure		Method
**Primary outcomes**		
	Effective PrEP^a^ use (biomarker assessment)	Percentage of all study participants with biomarker TFVdp^b^ levels indicating consistent PrEP use (≥4 doses per week) for the past 2 months. [68,69]. Represents a composite outcome of PrEP initiation and high execution to capture these key steps in the HIV prevention continuum. Collected at months 6 and 12 only.
**Secondary outcomes**		
	IPV^c^ prevalence	Percentage of participants reporting IPV since the last study visit, measured with the WHO VAWI^d^ [70] and classified by the STRIVE consortium definition [71]: any act of severe physical or sexual violence or ≥2 acts of moderate physical violence.
	IPV severity	Percentage of participants reporting any sexual or severe physical IPV since the last study visit, measured with WHO VAWI [70].
	IPV intensity	Continuous score calculated from the number of specific violent acts reported and the reported frequency of each act (0=never; 1=once; 2=a few times; and 3=often) since the last study visit, measured with WHO VAWI [70].
**Exploratory outcomes (subcomponents or alternate measures of primary and secondary outcomes)**		
	PrEP uptake	Percentage of participants initiating PrEP *among those not on PrEP at baseline*, self-reported and validated by Ministry of Health records.
	PrEP execution	Percentage of participants with TFVdp levels indicating consistent use *among those reporting current PrEP use.*
	PrEP persistence	Percentage of participants with any detectable TFVdp *among those who ever initiated PrEP.* Participants who self-report discontinuation will be categorized as having undetectable TFVdp levels.
	Recent PrEP use (biomarker)	Percentage of all study participants with biomarker FTCtp^e^ levels indicating consistent PrEP use (≥4 doses per week) for the past 2 wk. Collected at months 6 and 12 only.
	IPV type	Percentage of participants reporting each IPV type (physical, sexual, emotional, and economic) since the last visit, per WHO VAWI [70].

^a^PrEP; preexposure prophylaxis.

^b^TFVdp: tenofovir diphosphate.

^c^IPV: intimate partner violence.

^d^WHO VAWI: World Health Organization’s Violence Against Women instrument.

^e^FTCtp: emtricitabine triphosphate.

The secondary outcomes of the study will be the proportion of participants reporting any IPV and severe IPV (Table 4) between enrollment and month 6, and between month 6 and month 12, and the difference in IPV intensity scores at months 6 and 12. The aim 2 hypothesis is that the proportion of participants reporting any IPV and severe IPV and IPV severity scores will all be *lower* at both time points in the intervention arm versus control arm.

In exploratory analyses, we will first explore effect modification by age (15-19 vs 20-24) and DREAMS participation (current, former, or never) for the primary and secondary outcomes. Second, we will break down the primary outcome into steps along the continuum (PrEP uptake, execution, and persistence) and IPV outcomes by type—physical, sexual, emotional, and economic—to understand where the intervention had its strongest effects. Third, we will compare the proportion of participants per arm with emtricitabine triphosphate (FTCtp) levels indicating consistent PrEP adherence over the past 2 weeks. Comparing TFVdp and FTCtp levels will yield insights on adherence patterns over both a long and short window of time before collection. We will also analyze the alignment of adherence measures with HIV risk perception and behavior to better understand adherence patterns.

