## Discussion

### Innovations and Future Application

This study offers 4 key innovations. First, it offers the opportunity to address the lack of evidence-based interventions that explicitly confront the role of IPV and relationship dynamics in supporting PrEP use among adolescent girls and young women. Current interventions have focused largely on instrumental adherence support (eg, pill-taking reminders and strategies), motivational interviewing, and peer support, with limited evidence of success [4,5,78-83]. If found effective, the Tu’Washindi intervention will be one of the first to successfully address critical partner-related barriers to uptake and adherence and to directly involve male partners to build their support for PrEP use among adolescent girls and young women. Second, our intervention approach is youth-designed and tailored to meet the specific needs of adolescent girls and young women, qualities that have been specifically called for in recent literature to address shortcomings in existing interventions [84,85]. The intervention components of male engagement and couples’ education were added to the design in direct response to the formative research findings, and our participatory design methods resulted in high intervention acceptability and uptake among adolescent girls and young women and high ratings for relevance and perceived effectiveness. Third, our multilevel approach recognizes that IPV and relationship power create barriers to HIV prevention at the individual, partnership, and community levels. Tu’Washindi supports adolescent girls and young women to respond to experienced or anticipated IPV at each level by fostering self-efficacy, improving relationship communication, developing support systems, and encouraging action to maintain safety and HIV prevention adherence [86-88]. Fourth, we assess short- and long-term adherence with biomarker measurements of 2 active PrEP metabolites, TFVdp and FTCtp to gain a more thorough understanding of adolescent girls and young women adherence behavior. Although the field has focused on TFVdp levels to classify long-term (ie, previous 1-3 months) PrEP adherence [89], FTCtp concentrations can delineate between consistent (≥4 doses/week) versus inconsistent (<4 doses/week) PrEP adherence over 2 weeks before sample collection with ≥89% accuracy [90]. Thus, we will have the ability to classify adolescent girls and young women by short-term (2 weeks) adherence in addition to the long-term (2 months) adherence measured by TFVdp levels.

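### PrEP execution applies a 2-month TFVdp marker to all current users with no minimum time on PrEP, so late uptake is partly counted as poor execution

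*Protocol article*

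**What the plan says.** Table 4 (Exploratory outcomes) gives both parts of the execution measure. The numerator is "Percentage of participants with TFVdp levels indicating consistent use" and the denominator is women "among those reporting current PrEP use". No minimum time since starting is attached to either.

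The meaning of a consistent TFVdp result comes from the primary outcome row of the same table: "levels indicating consistent PrEP use (≥4 doses per week) for the past 2 months". The Discussion (Innovations and Future Application) repeats the window as "in addition to the long-term (2 months) adherence measured by TFVdp levels". Slightly earlier in that section it describes the field's general use of "TFVdp levels to classify long-term (ie, previous 1-3 months) PrEP adherence". Outcomes and Hypotheses says the laboratory will split the levels "to delineate between consistent (≥4 doses per week) versus inconsistent (<4 doses per week) adherence". These are two classes, and no allowance for time on drug is mentioned.

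Recent starters are sampled by design. Data Collection (cRCT Component) states: "DBS samples are collected via fingerprick at months 6 and 12 from all participants who report initiation or continuation of PrEP since the last visit". The preceding data collection visit is month 3 for the month 6 sample and month 6 for the month 12 sample. Eligibility Criteria admits both women already on PrEP and women who are only interested in it, so starts can occur at any point in follow-up.

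FTCtp, the 2-week marker, is measured at the same two visits. Table 4 defines its outcome over all study participants, not over current users.

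**The concern.** The exploratory analyses break the primary outcome into uptake, execution and persistence to show at which step the intervention acted. For that purpose, execution should describe how well a woman takes PrEP once she is on it. A marker that looks back 2 months cannot do this for a woman with only a few weeks of exposure. Two women with the same daily pill-taking, one who started 3 weeks ago and one who started 6 months ago, would receive opposite scores. The difference between them is when they started, which belongs to uptake.

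What is at stake is how the breakdown is read. Execution would be understated by an amount that depends on how many current users began recently, and a contrast between arms on execution would be partly a contrast in start dates.

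**Working it through.** There is no stated figure to reproduce, because this is an outcome definition. The check asks how long a woman must be on PrEP before the definition can class her as consistent.

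**Check 1: the article's own figures, doses averaged evenly over the window.** Inputs are the threshold of 4 doses per week and the window of 2 months, W = 8 to 8.7 weeks (both from Table 4). A woman taking d doses per week who started w weeks ago averages d × w / W. She reaches 4 when w ≥ 4W / d.

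- Daily use (d = 7): 4 × 8 / 7 = 4.6 weeks; 4 × 8.7 / 7 = 5.0 weeks.
- Exactly 4 doses per week: the full 8 to 8.7 weeks.

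Averages for a daily user with W = 8:

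| Weeks since start | Average doses per week | Class |
|---|---|---|
| 2 | 7 × 2 / 8 = 1.75 | inconsistent |
| 3 | 7 × 3 / 8 = 2.6 | inconsistent |
| 4 | 7 × 4 / 8 = 3.5 | inconsistent |
| 5 | 7 × 5 / 8 = 4.4 | consistent |

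With the wider 1 to 3 month window (W = 4.35 to 13 weeks), the crossover for daily users is 2.5 to 7.4 weeks.

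**Check 2: gradual accumulation (assumption).** The article gives no half-life, so I assume first-order accumulation with half-life h and a cut at the steady-state level for 4 doses per week. Days below the cut = h × log2(1 / (1 − 4/d)).

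| Half-life (days) | Daily use | 5 doses per week |
|---|---|---|
| 10 | 12 days | 23 days |
| 17 | 21 days | 40 days |
| 25 | 31 days | 58 days |

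The interval in which a daily user cannot pass is shorter than in Check 1 but does not vanish.

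**Check 3: how many women (assumption).** The timing of starts is not given. If on-study starts were even over follow-up, 2/6 = 33% of on-study initiators would have less than 2 months on PrEP at month 6, and 2/12 = 17% at month 12. For less than 1 month the shares are 1/6 = 17% and 1/12 = 8%. These are shares of initiators. Women already on PrEP at enrollment also sit in the denominator and lower the share among all current users.

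**Check 4: effect on the reported percentage (assumption).** Suppose true execution is 40% and a share r of current users, with the same true execution, cannot yet pass. Reported execution is 0.40 × (1 − r): 36% for r = 10%, 32% for r = 20%, 27% for r = 33%. The last is an upper-end illustration, since Checks 1 and 2 show that many women pass before 2 months.

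**The case against.** **A reader might infer a bias against the intervention arm**, on the ground that its activities prompt late starts. The documents do not support this. By Table 3 and Intervention Delivery, community sensitization is confined to months 1 to 3 and Buddy Days fall around month 3. Clubs meet twice monthly in months 1 and 2 and monthly after that, so five sessions are complete by month 3. In the sample order of Table 2 those five carry all the set PrEP and relationship topics; the rest are two open sessions and a closing one. Starts prompted by this schedule would mostly be more than 2 months old at month 6, and by month 12 activities have been over for 6 months. Uptake support is said to run through all club sessions, so some late starts remain possible. An imbalance could go either way or be absent.

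**A reader might also infer that every start within 2 months is miscoded.** That is not so: daily users pass after about 5 weeks in Check 1, or 12 to 31 days in Check 2. Only sampled users matter, too, because women followed up by phone or at a remote location give no DBS.

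**The measure is a subcomponent of the primary outcome.** Using the same TFVdp criterion keeps the two aligned. This stands, and is a reason to keep the measure and add to it.

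**The planned TFVdp and FTCtp comparison may expose recent starters.** It may help interpretation, but FTCtp is defined over all participants, so it mixes uptake with adherence again and does not repair execution.

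**A minimum exposure rule could sit in an analysis plan not shown, and the laboratory could allow for time on drug.** Either is possible. But Table 4 already states numerator and denominator, and as stated they produce the miscoding; the article describes no such allowance.

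**Any artefact may be small against the trial's precision.** At the upper ward SD of 10% in Sample Size Considerations, ward variation alone gives a 95% half-width of 1.96 × 0.10 × √(2/11) = 8.4 points for a difference between arms. This argues for a low severity; it does not make the definition right.

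**Conclusion.** The point holds as a minor flaw in an exploratory outcome. On the article's own threshold and 2-month window, a fully adherent daily user is classed as inconsistent until about 5 weeks after starting, and women taking fewer doses wait longer. Execution as defined therefore absorbs part of the timing of uptake.

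The 5-week figure assumes that doses are averaged evenly over the window; under the assumed half-lives of 10 to 25 days it is about 2 to 4 weeks for daily users. The share of women affected, and the size and direction of any difference between arms, cannot be determined from the documents. The figures in Checks 3 and 4 are illustrations only.

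The primary outcome is unaffected: it is taken over all participants, and use over the past 2 months is part of what it sets out to measure.

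**What to change.** Keep the TFVdp execution measure in Table 4 as the subcomponent of the primary outcome, and add three items:

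1. Report the same measure restricted to current users whose present PrEP episode began at least 2 months before the visit, dating the start or restart from the PrEP use history and the Ministry of Health records already used to validate uptake.
2. Report FTCtp-consistent use among current users from the same DBS, as a separate measure. Do not merge the two markers into one outcome.
3. Tabulate time since start or restart by arm at months 6 and 12.

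Base any statement about an intervention effect on execution on items 1 and 2, read alongside item 3. The primary outcome stays as it is.

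The cost is a few lines in the analysis plan and one derived variable; no new samples or assays are needed. The article expects data collection to run until May 2026, which allows this to be specified before the analysis. The downsides are somewhat fewer women in the restricted version, start dates that are partly self-reported, and a denominator that is still defined after randomization, so these comparisons remain descriptive.
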